### 4.5. Data Management

The data will be stored in REDCap (Harvard Catalyst, The Clinical and Translational Science Center). The project leader ([name]) will review it for correctness and plausibility in ca. 20% of the patients. The statistician will check the data also for plausibility before analyses.

## 5. Statistical Analyses

### 5.1. Primary Analyses

The baseline demographic, clinical, laboratory measures and cognitive scores will be compared between groups using an ANOVA for continuous variables and Chi-square tests for categorical variables. Covariates such as age and gender will be included if group differences exist at baseline.

A mixed-factorial ANOVA will be conducted to evaluate the effect of the rTMS protocol after 4 weeks of daily stimulation on plasma BDNF levels, the plasmatic EV-derived BDNF concentration, and EF performance. The model will include Group as a between-subjects factor and Time as a within-subjects factor.

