## 3. Materials

### 3.1. Laboratory Measurements, Neurocognitive Assessment, and TMS Intervention

#### 3.1.1. Blood Sampling

All the blood samples will be drawn in the morning after overnight fasting at three time points: before the start of rTMS intervention (baseline), within 1 week after the end of treatment (T1), and within 1 week after the maintenance period (T2).

Blood will be drawn by trained staff from the antecubital vein (gauge of needle: 21 G × ¾″ × 7″, BD Vacutainer, REF 367282; BD, NJ, USA) into 15 vacutainers to ensure sufficient sample collection. Possible confounders for BDNF levels such as sex, age, and BMI will be accounted by statistical analysis and by analyzing multiple measurements at different time points intra subjects.

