### 4.4. Power Analysis

The primary outcome measures will be plasma BDNF, plasmatic EV-derived BDNF, and BADS. We anticipate positive score changes in the R-Gr group, a minimal effect in the S-Gr group, and, aside from a slight learning effect regarding cognitive performance, no changes in the C-Gr group. This will effectively balance out in our analyses because we will compare changes in means across these groups.

We have estimated our sample size using G*Power 3.1 for a repeated-measures MANOVA with between-group factors. The parameters were set as follows: medium effect size (f = 0.25), significance level (α = 0.05), power (1 − β = 0.80), correlation among repeated measure (r = 0.1), 3 groups, and 3 repeated measurements. The calculation indicated a required total sample size of 66 participants (approximately 22 per group) to detect a significant difference between groups. To account for a 10% dropout rate, the adjusted total sample size will be 73 participants (approximately 24–25 per group). This sample size will ensure adequate power to detect clinically meaningful differences while accounting for potential attrition.

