### 5.2. Secondary Analyses

To assess the maintenance effect of rTMS 8 weeks post treatment on plasma BDNF, plasmatic EV-derived BDNF concentrations, and EF performance, separate mixed-factorial ANOVA models will be used. Group will serve as the between-subjects factor and Time (baseline, T2) as the within-subjects factor.

To evaluate the long-term effects of rTMS, a mixed-factorial ANOVA including Group as a between-subjects factor and Time (baseline, T1, T2) as a within-subjects factor will be performed. 

Relationships between plasma BDNF/plasmatic EV-derived BDNF values and EF performance scores post treatment (4 weeks) and at the 8-week follow-up will be explored using multivariate regression analysis, with adjustments made for confounders such as age, sex, and disease duration.

A Bonferroni correction will be applied to all mixed-factorial models to adjust for pairwise comparisons, minimizing the risk of the Type I error.

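### Section 5.1 lets chance baseline differences choose the covariates, and its Group × Time ANOVA forgoes the precision of adjusting for the baseline outcome

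*Protocol article*

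**What the plan says.** Section 5.1 first compares the randomised groups on baseline variables, which "will be compared between groups using an ANOVA for continuous variables and Chi-square tests for categorical variables". It then makes adjustment depend on the result: "Covariates such as age and gender will be included if group differences exist at baseline". No threshold for a difference is given, and the covariate list is open.

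For the primary comparison, "A mixed-factorial ANOVA will be conducted to evaluate the effect of the rTMS protocol after 4 weeks of daily stimulation", and "The model will include Group as a between-subjects factor and Time as a within-subjects factor". Section 5.1 does not list the levels of Time. Because it concerns the four-week effect, and Section 5.2 sets out the other models separately (one with "Time (baseline, T2) as the within-subjects factor", one with "Time (baseline, T1, T2) as a within-subjects factor will be performed"), the natural reading is baseline and T1. Baseline is thus a level of the response, not a covariate. Section 4.4 agrees: "we will compare changes in means across these groups".

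Two other places speak about covariates. Section 3.1.1 says "Possible confounders for BDNF levels such as sex, age, and BMI will be accounted by statistical analysis", and adds that repeated measurement within subjects will help. Section 5.2 adjusts its regression of executive function on BDNF for age, sex and disease duration, without condition. BMI is named in neither 5.1 nor 5.2.

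**The concern.** Under randomisation, baseline differences between groups arise by chance. A significance test on age or sex says nothing about whether that variable predicts BDNF or the BADS score, which is the reason to adjust. A trigger of this kind can bring in a covariate of no value and leave out a prognostic one. With no threshold and an open list, two analysts could fit different primary models to the same data, and the article offers three differently worded covariate rules to choose from.

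The second issue is efficiency. With two visits, the Group × Time interaction tests the difference in mean change, which subtracts the whole baseline value however weakly it predicts T1. Conditioning on baseline subtracts only the predictive part. With about 22 completers per group, that precision is worth having, and the data needed are already collected at T0.

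**Working it through.** **Inputs from Section 4.4.** f = 0.25, α = 0.05, power 0.80, r = 0.1, three groups, three measurements, N = 66 (22 per group), raised to 73 for dropout.

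**The plan's own figure.** For the between-groups test of a repeated-measures design, λ = f²·N·m/[1 + (m − 1)r] = 0.0625 × 66 × 3/1.2 = 10.31, with 2 and 63 degrees of freedom. Power is 0.808. The smallest N is 65, or 66 in equal groups, so the stated 66 reproduces. This tests group means averaged over three visits, which is not the test in Section 5.1.

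**How often the covariate rule fires by chance.** Assume a 0.05 threshold and k independent baseline tests (neither is in the article). The chance that at least one covariate enters under perfect randomisation is 1 − 0.95^k:

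- k = 2: 9.8%
- k = 5: 22.6%
- k = 10: 40.1%

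**Change score against baseline adjustment.** Assume equal SD σ at both visits, correlation r between them, and no true baseline difference.

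- Change score: variance 2σ²(1 − r).
- ANCOVA on baseline: residual variance σ²(1 − r²).
- Ratio, ANCOVA to change: (1 − r²)/[2(1 − r)] = (1 + r)/2, below 1 for every r < 1.

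**Power at N = 66.** Assume that f = 0.25 is the spread of T1 group means in T1 SD units. Then f²N = 0.0625 × 66 = 4.125. The noncentrality is 4.125/[2(1 − r)] for change (2 and 63 df) and 4.125/(1 − r²) for ANCOVA (2 and 62 df).

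| r | Variance ratio | λ change | λ ANCOVA | Power, change | Power, ANCOVA |
|---|---|---|---|---|---|
| 0.1 | 0.55 | 2.29 | 4.17 | 24% | 41% |
| 0.5 | 0.75 | 4.13 | 5.50 | 41% | 52% |
| 0.7 | 0.85 | 6.88 | 8.09 | 62% | 70% |
| 0.8 | 0.90 | 10.31 | 11.46 | 81% | 85% |

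The gain is 17 points at the plan's r and 4 points at r = 0.8. It shrinks but does not reverse.

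**Effect of the conditional rule on error rates.** A simulation (6,000 runs per setting, 22 per group, assumed correlation of 0.3 between age and the outcome at each visit, r = 0.1, 0.5 and 0.7) gave type I error of 0.045 to 0.052 for change with age added only when the groups differed. Its power equalled that of unadjusted change. In this set-up age relates equally to both visits and so cancels from the change, which limits how far the result generalises.

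**The case against.** The strongest reply is that nothing here invalidates the trial. A comparison of change is unbiased under randomisation, Section 4.4 announces it, and the conditional rule did not inflate type I error in simulation. All of this stands: the point is an unfixed model and forgone precision.

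The size also depends on assumptions. The article gives r = 0.1 only as a sample-size input. If the true baseline-to-T1 correlation is 0.7 or more, the gain is modest. Nor does the article say that f = 0.25 is a T1 effect, so the absolute powers illustrate the contrast between methods and are not a verdict on sample size. Larger gains appear if one posits an effect of about 0.8 SD (50% to 77% at r = 0.1), but that effect is nowhere in the article, and with it the gain at r = 0.7 is only 94% to 97%.

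Two stronger readings are tempting and not supported:

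- *Sections 3.1.1 and 5.1 flatly contradict each other.* Section 3.1.1 does not promise unconditional adjustment and also relies on within-subject measurement, while the open list in 5.1 does not exclude BMI. It is a tension that needs clarifying.
- *Patients with a missing visit will be dropped.* A reader might infer this from how mixed-factorial ANOVA is usually run, but the article does not state how missing visits are handled, and that may sit in the full protocol or analysis plan. For the baseline-to-T1 contrast, a patient without T1 would add almost nothing under a mixed model either.

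**Conclusion.** The point holds as one about prespecification and efficiency. The covariate rule in Section 5.1 makes the primary model depend on chance imbalance, and it should be reconciled with Sections 3.1.1 and 5.2. The planned baseline-to-T1 analysis is valid but has larger variance than baseline adjustment at any r below 1. At r = 0.1 the change-score analysis needs 1/0.55 = 1.82 times the patients for the same precision, at 0.5 it needs 1.33 times, and at 0.7 it needs 1.18 times. These ratios rest on equal SDs at the two visits and no true baseline difference; the powers rest also on reading f = 0.25 as a T1 effect. Only the covariate rule makes the model data-dependent; the choice of change score is purely a matter of precision.

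**What to change.** 1. In Section 5.1, analyse each primary outcome at T1 by ANCOVA with group, the baseline value of that outcome, age and sex, plus BMI for the two BDNF outcomes. State that these covariates enter irrespective of baseline differences.
2. In Section 5.2, use the same baseline adjustment for the T2 comparison.
3. Remove baseline significance tests as the trigger for covariates; a descriptive baseline table is enough.
4. Align Sections 3.1.1, 5.1 and 5.2 so that the covariates named in each place agree or the difference is explained.

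The cost is wording and a few degrees of freedom: three for BADS (baseline, age, sex) and four for the BDNF outcomes, leaving 66 − 3 − 3 = 60 and 66 − 3 − 4 = 59 for error. No new data are needed beyond recording BMI, which Section 3.1.1 already relies on. Recruitment has begun and Section 5.3 plans an interim look at efficacy at 50% enrolment, so the model should be fixed before outcome data are seen.

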### 5.2. Secondary Analyses

To assess the maintenance effect of rTMS 8 weeks post treatment on plasma BDNF, plasmatic EV-derived BDNF concentrations, and EF performance, separate mixed-factorial ANOVA models will be used. Group will serve as the between-subjects factor and Time (baseline, T2) as the within-subjects factor.

To evaluate the long-term effects of rTMS, a mixed-factorial ANOVA including Group as a between-subjects factor and Time (baseline, T1, T2) as a within-subjects factor will be performed. 

Relationships between plasma BDNF/plasmatic EV-derived BDNF values and EF performance scores post treatment (4 weeks) and at the 8-week follow-up will be explored using multivariate regression analysis, with adjustments made for confounders such as age, sex, and disease duration.

A Bonferroni correction will be applied to all mixed-factorial models to adjust for pairwise comparisons, minimizing the risk of the Type I error.

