#### 4.3.2. Exclusion Criteria

Participants will be excluded if they meet any of the following conditions:1.Advanced disease stages
Hoehn and Yahr stages ≥ 4, indicating severe disease progression with significant motor and cognitive impairment.
2.Neurological and psychiatric comorbidities
Any neurological condition other than PD;A history of major psychiatric disorders, including major depressive disorder (Beck Depression Inventory-II ≥ 29 [37] or active psychosis, which could confound cognitive assessments;Transient ischemic attack, stroke, or any unexplained loss of consciousness or severe ongoing stressor within 1 year prior to screening.
3.Contraindications to rTMS
Contraindication to treatment will be investigated using a standard safety questionnaire to screen potential subjects for risk of adverse events during TMS (Safety Questionnaire for TMS [38]);Presence of metallic implants, pacemaker, or other electronic medical devices that pose a safety risk during TMS session;History of epilepsy or seizure disorders, as determined by self-reporting and medical history.
4.Others
Any medical conditions that are not stable or controlled, or, which in the opinion of the Investigator, could affect the subject’s safety or interfere with the study assessments and treatment;Any medications that, in the opinion of the Investigator, may contribute to cognitive impairment, put the subject at higher risk for adverse events, or impair the subject’s ability to perform cognitive testing or complete study procedures.Use of illicit narcotic medication.

Patients who fulfill the inclusion criteria and do not meet any exclusion criteria will be asked to enroll in the project.

Once enrolled, patients will be randomly assigned to one of three groups: (1) R-Gr, (2) S-Gr, or (3) C-Gr. A computerized random number generator (www.random.org/sequences/, accessed on 24 January 2025) with concealment, with a 1:1:1 allocation, will be used for randomization. Blood collection and neurocognitive assessment will be performed at baseline, T1, and T2.

The assessment will be conducted in one session and it will take 60 min for each patient. Schedule of study procedures is reported in Table 1.

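### The stated Bonferroni correction does not act across the three primary outcomes, so Type I error control depends on an unstated success rule and the stated power holds for one outcome only

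*Protocol article*

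**What the plan says.** Section 2.1 lists three primary outcomes under separate headings, and section 4.4 repeats them: "The primary outcome measures will be plasma BDNF, plasmatic EV-derived BDNF, and BADS". None is placed first, and no passage says whether one, some or all must succeed.

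Section 4.4 gives alpha once. The inputs are "medium effect size (f = 0.25), significance level (α = 0.05), power (1 − β = 0.80), correlation among repeated measure (r = 0.1), 3 groups, and" three repeated measurements, for "We have estimated our sample size using G*Power 3.1 for a repeated-measures MANOVA with between-group factors". The result is 66 patients in total, raised to 73 for dropout.

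Section 5.1 plans a mixed-factorial ANOVA of Group by Time "on plasma BDNF levels, the plasmatic EV-derived BDNF concentration, and EF performance". It states no test level and does not say which pair of groups is decisive.

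The only multiplicity rule closes section 5.2: "A Bonferroni correction will be applied to all mixed-factorial models to adjust for pairwise comparisons, minimizing the risk of the Type I error".

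**The concern.** Multiplicity enters this plan in two directions: three groups give several pairwise comparisons within each outcome, and there are three primary outcomes. The stated Bonferroni correction deals with the first. Nothing shares alpha across the outcomes, orders them or requires them all, yet the sentence is worded as if Type I error were dealt with as a whole.

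Two things are at stake. First, a significant result on one biomarker could be reported as a positive primary finding although BADS, the only cognitive primary outcome, showed nothing. The chance of such a claim arising by luck can exceed 5%. Second, the sample size rests on one test at 0.05. Once alpha is shared across three outcomes, the stated 80% power no longer describes any one of them.

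**Working it through.** **Inputs.** From section 4.4: f = 0.25, alpha = 0.05, power 0.80, r = 0.1, k = 3 groups, m = 3 measurements, N = 66 (22 per group). From section 4.3.2: 1:1:1 allocation. Assumed, because the article does not give them:
- the correlation between the three outcomes (0 to 0.9 shown)
- success if any one primary outcome is significant
- three pairwise comparisons per model for the Bonferroni correction, so 0.05/3 = 0.0167 per pair

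**Step 1: reproduce the plan's figure.** For the between-group effect in a repeated-measures design, λ = f² × N × m / (1 + (m − 1) × r), with k − 1 and N − k degrees of freedom.

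At N = 66, λ = 0.0625 × 66 × 3 / (1 + 2 × 0.1) = 12.375 / 1.2 = 10.31 on 2 and 63 df. At alpha 0.05 the power is 0.808. The smallest sufficient N is 65, or 66 with equal groups. The stated 66 therefore reproduces as one outcome tested once at an undivided 0.05.

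**Step 2: closed form for three outcomes.** Three independent tests at 0.05 give 1 − 0.95³ = 0.1426. The upper bound under any dependence is 3 × 0.05 = 0.15.

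**Step 3: simulation under the null.** 100,000 trials, 22 per group, normal change scores, three outcomes with equal pairwise correlation. The entries give the chance of at least one false primary claim, by the test that carries the claim. The Monte Carlo standard error is about 0.1 percentage point (√(0.14 × 0.86 / 100,000) = 0.0011).

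| Correlation | Any omnibus F at 0.05 | Any Bonferroni-adjusted pair | Real vs sham or real vs no treatment, each at 0.0167 | Real vs sham only, at 0.0167 |
|---|---|---|---|---|
| 0 | 14.3% | 12.6% | 9.2% | 4.9% |
| 0.3 | 13.5% | 11.9% | 8.6% | 4.7% |
| 0.5 | 12.6% | 11.2% | 8.1% | 4.4% |
| 0.7 | 11.2% | 9.8% | – | – |
| 0.9 | 8.5% | 7.5% | – | 3.0% |

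The last column follows from simple arithmetic: three outcomes at 0.0167 each cannot exceed 3 × 0.0167 = 5%.

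**Step 4: power when alpha is shared.** With the formula of step 1 at alpha 0.05/3 = 0.0167, power at N = 66 is 0.66. With equal groups, 80% power needs N = 87, for which λ = 0.0625 × 87 × 3 / 1.2 = 13.59. With 10% dropout that is 87 / 0.9 = 96.7, so 97.

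**The case against.** The strongest counter-argument is that the existing pairwise correction may already be enough. If the claim rests on real versus sham alone, and each model has three adjusted pairs, the family-wise error across the three outcomes is 5% or less. This stands, and it limits the point. An omnibus F does not in itself show that real stimulation beat sham, so the highest figures apply only if that test carries the claim. A reader might infer that the primary error rate is simply 13–15%, or nearly three times nominal. The article does not support that as a general statement, because it fixes neither the decisive contrast nor the number of comparisons.

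Two further readings go beyond the text:
- **Any one significant outcome counts as success.** No such rule is stated. The aim at the end of the Introduction joins the two BDNF measures and executive function with 'and'. A rule requiring all three would cause no inflation, but it is not stated either.
- **Each outcome is tested at 5% in its own model.** Alpha 0.05 appears only in the sample-size paragraph. Section 5.1 speaks of one mixed-factorial ANOVA, and separate models are named only for the follow-up analyses in 5.2. Separate models are still the likely reading, since the outcomes are on different scales.

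The MANOVA in 4.4 is no rescue. Its inputs describe repeated measurements over time, and section 5 plans ANOVA, not a joint test of the three outcomes.

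It can also be said that an alpha rule across outcomes belongs in the statistical analysis plan, which is not shown. That would answer silence. Here the article states a rule, limits it to pairwise comparisons and claims Type I error control from it.

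**Conclusion.** The point holds in limited form. The plan names three unranked primary outcomes and a correction that does not act across them, so its statement on Type I error is too broad. The size of the problem depends on a choice that the article leaves open. If any one outcome suffices, and for correlations of 0 to 0.5, the family-wise error is about 13–14% by omnibus F, 11–13% by any adjusted pair and 8–9% by real versus either control. It is about 5% or less by real versus sham alone with three comparisons per model. Stronger correlation lowers all of these.

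The firmer consequence concerns power. The 0.81 at N = 66 belongs to one outcome at alpha 0.05. At 0.05/3 it is about 0.66 per outcome. These figures keep the protocol's own effect size, correlation and type of test. They do not include the interim look at efficacy in section 5.3.

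**What to change.** - **Section 5.1:** name real versus sham at T1 as the primary contrast for each outcome. Test the three contrasts as one family by Holm at a family-wise two-sided 5%. Test real versus no treatment for an outcome only if its real versus sham test succeeded. Let this replace the pairwise Bonferroni correction for the primary analysis.
- **Level of the gated tests:** state it, or label these tests supportive. The Holm 5% covers the three real versus sham contrasts. Three gated tests at 0.05 each could add error of up to 3 × 0.05 = 15% among themselves.
- **Section 5.2:** correct the Type I error sentence so that it claims only what the pairwise correction does.
- **Section 4.4:** restate the power per outcome at the level used.

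A single designated primary outcome, a fixed order or an all-three rule would also close the gap. Whichever is chosen should be fixed before the interim analysis, since the article says that recruitment has begun.

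The cost is wording, plus a less favourable power statement: about 0.66 per outcome at N = 66, or 87 patients (97 with dropout) to restore 80% on the protocol's inputs. The real versus sham contrast itself loses little or nothing. With three comparisons per model the existing Bonferroni correction already tests it at 0.0167, which is also Holm's first step.

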### 5.3. Interim Analysis

Data accumulation and treatment efficacy will be monitored through an interim analysis upon 50% enrollment to identify potential issues early.

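### Section 5.3 plans an efficacy look at 50% enrolment, neither barring an early stop or claim nor setting a boundary, while the sample size puts the full α = 0.05 on a single test

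*Protocol article*

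**What the plan says.** Section 5.3 of the protocol article is one sentence: "Data accumulation and treatment efficacy will be monitored through an interim analysis upon 50% enrollment to identify potential issues early". Efficacy is therefore part of the look, and the trigger is enrolment. The section gives no boundary and no rule for an early stop or claim. It also does not say who would see the results or whether they would be split by arm.

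Section 4.4 sets the sample size with "significance level (α = 0.05" and "power (1 − β = 0.80", and makes no allowance for a second test. The only Type I error control stated is in section 5.2: "A Bonferroni correction will be applied to all mixed-factorial models to adjust for pairwise comparisons". That deals with comparisons between groups, not with testing the same outcome twice over time.

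Section 4.1 describes the study as double-blind and single-centre and places T1, the primary time point, 4 weeks after baseline. Section 3.1.1 allows T1 blood to be drawn up to 1 week after treatment ends.

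**The concern.** Three features of the text do not fit together.

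- **Content and purpose.** The stated aim is to spot problems early. Slow recruitment, dropout, assay failures, poor data and safety signals can all be seen without comparing efficacy between arms.
- **Error rate.** An efficacy test at half-way followed by another at the end gives two chances of a false positive. Unless the first cannot lead to a stop or claim, or has its own boundary, the 5% level no longer describes the procedure.
- **Trigger.** The primary outcomes are changes at 4 weeks. If data are cut when half the patients are enrolled, the most recent entrants have no T1 value, so less than half of the primary information is available.

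Arm-level efficacy results seen mid-trial could also influence recruitment and treatment delivery in the second half, and that cannot be undone.

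**Working it through.** **1. Reproduce the sample size.** Inputs from section 4.4: "medium effect size (f = 0.25", "correlation among repeated measure (r = 0.1), 3 groups, and 3 repeated measurements", α = 0.05, power 0.80; "We have estimated our sample size using G*Power 3.1 for a repeated-measures MANOVA with between-group factors". The between-groups formula is

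λ = N·f²·m / (1 + (m − 1)ρ), df1 = k − 1, df2 = N − k.

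With N = 66, f = 0.25, m = 3, ρ = 0.1 and k = 3: λ = 66 × 0.0625 × 3 / 1.2 = 10.31, df = 2 and 63. Power at α = 0.05 is 0.808. The smallest N reaching 0.80 is 65, or 66 with equal groups. This matches the article: "The calculation indicated a required total sample size of 66 participants (approximately 22 per group". The figure is thus obtained by spending all of 0.05 on one test.

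**2. Error if either look can reject at 0.05.** This rule is an assumption; the article does not state it. For a two-sided z test at information fraction t, the two statistics have correlation √t, and

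Type I error = 1 − P(|Z₁| < 1.96 and |Z₂| < 1.96).

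| Information at the look | Method | Type I error, one outcome |
|---|---|---|
| t = 0.50 | z test | 0.083 |
| t = 0.50 (11 then 22 per group) | simulated three-group F | 0.084 |
| t = 0.40 | z test | 0.086 |
| t ≈ 0.36 (8 then 22 per group) | simulated three-group F | 0.090 |
| t = 0.25 | z test | 0.091 |

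Each simulation used 300,000 null trials. The rows below 0.50 are assumed values, covering the case where some enrolled patients lack T1.

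**3. Error if the look cannot lead to rejection.** The final F test alone rejected in 0.0495 of the simulated null trials. That is 0.05 within simulation error, so there is no inflation.

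**4. Timing.** Half of 73 is 36.5, so the trigger falls at 36–37 patients. Anyone enrolled in roughly the preceding 4 to 5 weeks would lack T1 if data were cut that day. The accrual rate is not given, so their number cannot be computed.

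**5. What the look could show.** With 33 patients analysed and the protocol's own assumptions, power at 0.05 is about 0.47. A non-significant interim result would be about as likely as a significant one even if the planned effect were real.

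**6. Boundaries that hold 0.05 overall (one outcome, t = 0.5).**

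| Rule | Interim level | Final level | Overall error | Power of final test, N = 66 |
|---|---|---|---|---|
| Haybittle–Peto | 0.001 | 0.05 | 0.0502 (z), 0.0500 (F) | 0.808 |
| O'Brien–Fleming type | 0.0052 | 0.048 | 0.050 (z), 0.0501 (F) | 0.803 |
| Pocock | 0.0294 | 0.0294 | 0.050 (z) | 0.740 |

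Under the Pocock rule, a single final test at 0.0294 would need about 75 patients for 80% power. The choice of boundary therefore decides whether 66 remains enough.

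**The case against.** The strongest reply is that the article describes monitoring, not a stopping rule. It states no early stop, early claim or design change, and a look that cannot lead to rejection costs no alpha (step 3). Boundaries and access to interim results are commonly set out in a full protocol or SAP, which are not shown, so their absence here is not in itself a defect.

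Much of this stands, and it rules out several stronger readings:

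- *That the plan inflates Type I error.* A reader might infer this, but it depends on a decision rule the article does not contain.
- *That the final test is stated to be at 0.05.* The 0.05 appears only as a sample-size input. Taking it as the final level is reasonable but is an inference.
- *That arm-level results will be exposed.* The text does not say so. Section 3.2 keeps the neuropsychologist blind to group, section 4.3.2 conceals allocation, and two of the three primary outcomes are laboratory measurements. Aggregate results would not reveal an individual's allocation. Exposure is a risk, not a stated fact.
- *That the chance of a false positive is above 20%.* Three independent outcomes each tested twice give 1 − (1 − 0.084)³, about 23%. But three tested once, with no interim, already give 1 − 0.95³ = 14.3%. Most of the total belongs to the separate multiplicity of three primary outcomes.
- *That T1 data will certainly be missing at the look.* This holds only if data are cut when the trigger is reached, and the article does not fix the cut.

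The reply does not remove what the article itself fixes: efficacy is named as content of the look, the trigger is enrolment, the sample size has no room for a second test, and the stated purpose does not need a between-arm comparison.

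**Conclusion.** The point holds in conditional form. The article commits to an efficacy look, does not rule out a stop or claim on it, sets no boundary, and sizes the trial as if there were one test. If nominal significance at 0.05 at the interim could end the trial or be claimed, Type I error per outcome would be 0.083–0.091 instead of 0.05, for information fractions of 0.50 down to an assumed 0.25. If it could not, the error stays at 0.05. These figures also assume that the final test is at 0.05. The enrolment trigger and the possible exposure of results by arm are further weaknesses whose size cannot be worked out from the article.

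**What to change.** Preferred change, in section 5.3: limit the 50% review to recruitment, retention, assay and data quality, and safety, on pooled data with no between-arm efficacy test. This serves the stated purpose and costs no alpha, power or patients. The only loss is an informal early read of efficacy, which at about 0.47 power would tell the team little.

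If an efficacy look is kept, section 5.3 should:

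1. trigger it when half the patients have completed T1, not when half are enrolled;
2. keep results by arm from the study team, for example by having a statistician outside it run the analysis;
3. either state that the look cannot lead to an efficacy stop or claim, which leaves the final level at 0.05, or name a boundary.

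Two boundaries leave N = 66 adequate: Haybittle–Peto (p < 0.001 at the interim, 0.05 at the end) and an O'Brien–Fleming type (0.0052, then 0.048), which lowers the power of the final test from 0.808 to 0.803. The O'Brien–Fleming levels were solved for t = 0.5 and must be recalculated if the look falls elsewhere. All levels are per outcome and do not address the multiplicity of three primaries.

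The change is a few sentences at most. Section 6.3 says recruitment has begun, so it should be made before the trigger is reached.
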